## Abstract

**Introduction:**

Parkinson’s disease (PD) is the second most common neurodegenerative disorder, its principal symptom being deterioration of motor function. Current treatment options are limited to symptom management but there is evidence that physical activity can provide motor benefits. More recently there is evidence to suggest that rhythmic auditory stimulation may improve gait and balance in PD. Sparky Samba is a community initiative in South Wales, UK, founded by a person living with PD. Sessions incorporate the following samba rhythms from a trained facilitator and are held weekly in a community setting.

**Methods:**

The Sparky Samba trial is a multi-site, non-blinded, randomised controlled feasibility trial of Sparky Samba compared with activity as usual. A total of 60 people with PD will be randomised 1:1 to take part in a local Sparky Samba group for 12 weeks or continue their normal activities for the same length of time. The primary outcome is feasibility defined by recruitment, retention, data completeness and intervention adherence. Secondary outcomes relating to motor function, cognition, well-being and self-efficacy will also be assessed at baseline and at 12 weeks. Additionally, we will conduct a process evaluation to understand contextual mechanisms surrounding Sparky Samba. This will be achieved through qualitative interviews and structured participant questionnaires following individual trial completion and through structured questionnaires with intervention delivery staff, supplemented with qualitative interviews.

**Analysis:**

Feasibility outcomes will be assessed according to pre-defined criteria. For secondary outcomes, means and standard deviations (or medians and IQRs) will be calculated by arm, alongside 95% CIs for change from baseline to 12-week follow-up. Qualitative data will be subject to thematic analysis using NVivo software.

**Ethics and dissemination:**

This study received a favourable ethical opinion from the North of Scotland Research Ethics Committee in April 2025 (REC reference 25/NS/0037). Study results will be disseminated through the peer-review literature, the ISRCTN registry and directly to participants, which will be facilitated by the study’s public and patient involvement steering group.

**Trial registration number:**

ISRCTN11861663

STRENGTHS AND LIMITATIONS OF THIS STUDYThis feasibility study originated from a person living with Parkinson’s disease.The trial design has included significant co-development with public and patient representatives.Inclusion of the process evaluation provides granular assessment of operational feasibility.The comparator condition (usual daily activities) will be highly variable between individuals.The activities as usual comparator does not fully control for the social interaction component of Sparky Samba.

## Introduction

 Parkinson’s disease (PD) is the second most common neurodegenerative disorder after Alzheimer’s disease, causing cell loss in the brain largely due to the abnormal aggregation of the alpha-synuclein protein. In PD, atrophy of dopaminergic cells in the substantia nigra leads to progressive decline of motor function alongside changes in cognition, sleep, mood and other non-motor symptoms. There are no disease-modifying therapies, with pharmacological treatment options primarily supporting motor symptom management and often with significant side effects that worsen other PD symptoms. Stakeholder research prioritisation exercises demonstrate the need for developing non-pharmacological interventions that may aid both motor and cognitive functions^1
2^ and allow tailoring for disease stage.^3^

Common non-pharmacological interventions shown to have both motor and non-motor benefits for people with PD (PwP) include physical activity in the form of targeted exercise^4
5^ or dancing^6^ and neurological music therapy techniques such as rhythmic auditory stimulation (RAS).^7^ RAS involves the synchronisation of walking pace to external rhythmic beats and has shown promising effects on gait and mobility in PwP.^8–10^ The majority of these interventions have been trialled in clinical settings, but it is recognised that community-based activities promoting healthy behaviours in PwP are likely to have greater long-term impacts^11–13^ due to their enhanced accessibility and effects of social cohesion.

A recently established PD-specific samba percussion group in South Wales, UK, called ‘Sparky Samba’, is a patient initiative designed and led by PwP for PwP and supported by a samba percussion tutor. This group’s activity combines rhythmic upper and lower limb activities with social stimulation. Awareness of Sparky Samba has gained momentum among PwP who have indicated a need for similar groups in other local communities across the region. An initial qualitative evaluation of Sparky Samba, conducted by our group (unpublished data), has highlighted its utility as a community-based activity for PwP with the potential to improve social connectedness, well-being, physical activity participation and cognition. As indicated by our trial research partner (the founder of Sparky Samba), PwP have expressed a preference for therapeutic activities and lifestyle interventions that they themselves can control. Patient-led research is essential to develop interventions that have a better chance of successfully translating into practice because they are inherently acceptable, meaningful and relevant to those they have been developed by and for.^14–16^

We have conducted an ethnographic study of the existing Sparky Samba group in Cardiff, with follow-up stakeholder workshops in order to: (1) identify core intervention components, including duration, type of exercises, movements, resources, delivery and specific content in preparation for intervention delivery; (2) refine intervention components and determine intervention flexibility and how this may be adapted for individuals; (3) describe and specify the resulting intervention in detail according to the TIDieR framework^17^ and (4) create a logic model and identify a ‘theory of change’ regarding intervention mechanisms (how it may work) and identify what may impact those mechanisms of change.

Sparky Samba has achieved support from the PD community (both PwP and the UK’s leading PD charity, Parkinson’s UK (PUK)) and arts-based funders but it warrants further investigation for its potential health benefits. The Sparky Samba intervention will be compared with an activities as usual control group. Our PD community members have indicated many people take part in other PD-specific groups, such as seated bowling or choirs, which have a similar duration to Sparky Samba sessions but are sporadic in their geographic availability. By using an activities-as-usual control, we aim to differentiate between the community and social aspects of standard social activities versus the specifics of the Sparky Samba intervention and potential benefits of rhythmic-based activities.

The aim of this study is to evaluate the feasibility of Sparky Samba in a small-scale randomised controlled trial (RCT) as a next step towards a full effectiveness evaluation of Sparky Samba as a health intervention for PwP.

## Methods and analysis

### Public and Patient involvement

The Sparky Samba groups were founded by a person living with PD. The initiative commenced with a single group in South Wales, which has now expanded to three groups across Wales. As a result of the benefits that initial group members perceived from participation, they sought to engage with robust scientific evaluation, forming a collaboration with academic and clinical researchers to develop this trial. Subsequently, the original Sparky Samba group have remained engaged throughout the process of developing and delivering this research. Therefore, not only is the Sparky Samba trial driven by the patient voice, but it is an integral factor in its ongoing delivery. The founder of Sparky Samba aided in securing funding for the trial and continues to engage through regular trial management group (TMG) meetings, along with an additional person who lives with PD. Additionally, the original Sparky Samba group members attended a series of three workshops to discuss and refine trial design, help with the selection of outcome measures and aid in defining the parameters for intervention adherence. They have also been involved in the development of patient-facing materials as well as intervention refinement. At the conclusion of the trial, we will work with this group on generating resources to communicate the trial results to the PD community alongside the development of a patient-focused dissemination strategy.

### Trial design and setting

The Sparky Samba trial is a parallel-group feasibility RCT of the Sparky Samba intervention compared with an activities-as-usual control group. We will recruit 60 PwP to be randomised 1:1 to the intervention or activities as usual for a period of 12 weeks. The recruitment target of 60 has been selected in line with guidance for sample sizes in feasibility studies.^18^ This sample size will allow estimation of recruitment, retention, adherence and data completeness rates with a 95% binomial CI of no more than plus or minus 13 percentage points irrespective of the point estimate. The trial is not powered for hypothesis tests to detect effects in the clinical outcome measures.

The trial will be conducted in three secondary care (National Health Service (NHS)) sites across Wales, UK, with the Sparky Samba intervention delivered at three local community sites identified and supported by the Sparky Samba group. The clinical sites have been selected due to their co-location with the Sparky Samba groups to facilitate attendance of participants at the Samba groups.

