### Randomisation

Participants will be randomised to the intervention or activities as usual in a 1:1 ratio, stratified by disease burden using the Hoehn and Yahr score of disease stage.^21^ The randomisation sequence, generated by the non-blinded, senior trial statistician, using nQuery software and stored securely so those enrolling participants cannot access it, will use permuted blocks of randomly varying sizes. The randomisation will be implemented via REDCap, and allocation to groups will be performed by the central trial team. Allocation will be communicated directly to the participant with concurrent notification to the recruiting site and, if required, the relevant local Sparky Samba group. Randomisation should occur within 14 days of the baseline assessment.

Owing to the nature of the intervention, this is a non-blinded trial. However, the trial statistician will remain blind to allocation until analysis is complete. Further, the Unified Parkinson’s Disease Rating Scale Part III^22^ will be video recorded, and ratings will be performed by a trained clinician blind to the allocation of the participant.

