### Activities as usual

Participants randomised to the activities as usual control group will be asked to continue with their normal activities and attend any social or support groups they would ordinarily participate in over the 12 weeks. Participation in the trial does not necessitate prior or ongoing attendance at a particular social or support group. A physiotherapy or physical activity control group was considered to control for the type of movement included in a Sparky Samba session. However, this was discounted because while there is good evidence that physiotherapy and exercise can benefit PwP,^23
24^ the delivery of physiotherapy and exercise to this patient group, either through healthcare systems or community groups, is inconsistent across the region. Further, in conjunction with our PPI group, we were conscious that the opportunity for social interaction was a key aspect of attending Sparky Samba, which would not be achieved through attendance at healthcare-delivered physiotherapy sessions. The PPI group also suggested that many PwP are involved in other local community groups; therefore, activities as usual was chosen as the control. From the input of the PPI group, we anticipate that activities as usual may consist of activities such as walking, the gym, seated bowls or less physically orientated activities such as a Parkinson’s choir. Given the varied availability of specific Parkinson’s groups or organised community groups, we have not specified activities as usual but will be asking people randomised to this group to specify the activities they have taken part in over the 12-week trial period. This will help us determine the feasibility of using ‘activities as usual’ as a comparator condition in a future effectiveness trial of Sparky Samba. Following completion of the 12-week follow-up assessment, participants randomised to activities as usual will be offered the opportunity to join their local Sparky Samba group. As for trial participants initially randomised to the intervention group, any costs associated with attendance at the Sparky Samba group will be supported by the trial for a period of 12 weeks.

During the intervention delivery period, there are no restrictions imposed on any additional treatment participants may require for their PD or otherwise. If changes in health status and/or treatment affect their participation in the trial, this will be recorded via notification of withdrawal.

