### Outcomes

The primary outcome for this trial is feasibility as defined by participant recruitment, retention, intervention adherence and data completeness according to pre-specified criteria. Thresholds for the feasibility criteria are detailed in table 1.

**Table 1 T1:** Measures of feasibility and pre-defined criteria for success used to determine the primary outcome

Variable	Progression criteria		
	Red	Amber	Green
Recruitment			
% of people approached who are willing to participate (100*(number consented/number approached)%)	<5%	5–19.9%	≥20%
Number recruited	<25	25-44	45-60
Retention			
% of participants attending the primary 12-week endpoint assessment (100*(number attending/number consented)%)	<50%	50–89.9%	≥90%
Adherence			
% of participants adherent to the intervention (attending ≥8 sessions) (100*(number adherent/number consented)%)	<50%	50–79.9%	≥80%
Data completeness			
% of participants completing at least 90% of baseline measures (100*(number completing ≥90%/number consented)%)	<70%	70–94.9%	≥95%
% of participants completing at least 90% of follow-up measures (100*(number completing ≥90%/number consented)%)	<50%	50–74.9%	≥75%

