### Analysis

Key demographic data will be summarised using descriptive statistics. For feasibility outcomes, recruitment will be assessed as the percentage of people approached who provide consent to participate in the trial; retention as the percentage of participants recruited who attend the 12-week follow-up assessment (primary endpoint); adherence as the percentage of participants adherent to the intervention (where intervention adherence is defined as attending ≥8 of 12 sessions) and data completeness as the percentage of participants completing ≥90% of baseline and follow-up measures, respectively (table 1). Feasibility criteria will be assessed according to a traffic light system with green (proceed to full effectiveness RCT) if all criteria listed in table 1 are in the green zone; amber (requiring adjustment before proceeding to full RCT) if all criteria are either in the amber or green zone; and red (do not progress to full RCT unless major changes are implemented) if at least one criterion is in the red zone. For secondary outcome measures, we will calculate descriptive summaries by arm, such as mean and standard deviation (or median and IQR, in case of a distinctly non-normal distribution) and 95% CIs of participants’ changes from baseline to 12-week follow-up. This will provide estimates of effect size and variability of drumming-induced changes for use in power calculations for a future large-scale RCT. No sub-group, sensitivity or interim analyses will be conducted. Reporting of results will follow the Consolidated Standards of Reporting Trials (CONSORT) guideline extension for pilot and feasibility studies.^26^ The statistical analysis plan will be available via ISRCTN (*ISRCTN11861663*).

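### The ±13-point precision claimed for all four feasibility rates does not hold for adherence, which rests on about 30 people and can be as imprecise as about ±18 points

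*Protocol article*

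**What the plan says.** Trial design and setting fixes the size and the allocation: "We will recruit 60 PwP to be randomised 1:1 to the intervention or activities as usual for a period of 12 weeks". Randomisation repeats the ratio. The size is said to follow guidance for feasibility studies, and a precision statement comes next. It names all four rates and gives them one bound, "estimation of recruitment, retention, adherence and data completeness rates with a 95% binomial CI of no more than plus or minus 13 percentage points", which is said to hold whatever value is observed.

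The Analysis section describes "adherence as the percentage of participants adherent to the intervention (where intervention adherence is defined as attending ≥8 of 12 sessions". Table 1, under Outcomes, gives the formula as the percentage "of participants adherent to the intervention (attending ≥8 sessions) (100*(number adherent/number consented", with red below 50%, amber from 50% to 79.9% and green from 80%.

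Two other sections settle who can count as adherent. Recruitment and consent excludes anyone who has ever taken part in a Sparky Samba group. Activities as usual says when controls may join: "Following completion of the 12-week follow-up assessment, participants randomised to activities as usual will be offered the opportunity to join their local Sparky Samba group".

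**The concern.** One worst-case bound is given for four rates that do not share a denominator. Retention and data completeness are measured in everyone who enters. Adherence to Sparky Samba can arise only in the arm asked to attend it, which is half the sample. A bound calculated for 60 people is too narrow for 30.

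Adherence is one of the components of the primary feasibility outcome, and under the Analysis section a single red criterion makes the whole result red. The ±13 figure is also the only number offered in support of a sample of 60. A reader who attached it to an observed 80% would take adherence to lie between 67% and 93% and would be too confident about the lower end.

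**Working it through.** **Inputs.** Total 60, allocated 1:1 (Trial design and setting; Randomisation). This gives 60/2 = 30 in the intervention arm. The article does not print the 30, and stratified blocks may shift it by a few. The claimed bound is 13 points at 95% for any point estimate (Trial design and setting). The adherence thresholds are 50% and 80% (Table 1).

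**Formula.** Normal-approximation half-width = 1.96 × √(p(1 − p)/n), which is largest at p = 0.5.

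**Step 1: reproduce the stated figure.** With n = 60, 1.96 × √(0.25/60) = 0.1265, or 12.65 points, which agrees with a bound of 13. The smallest n that gives ±13 is (1.96/0.13)² × 0.25 = 56.8, so 57. The exact (Clopper-Pearson) maximum half-width at n = 60 is 13.19 points, which meets the bound only after rounding. The stated figure is therefore the n = 60 figure.

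**Step 2: adherence in the intervention arm.** With n = 30, 1.96 × √(0.25/30) = 0.1789, or 17.9 points. This is 12.65 × √2, as expected when the denominator is halved. Other methods at n = 30:

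| Method | Worst-case half-width (points) |
|---|---|
| Wilson | 16.9 |
| Normal approximation | 17.9 |
| Exact | 18.7 |
| Continuity-corrected | 19.6 |

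None gives 13 or less.

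**Step 3: precision at the thresholds.**

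- Red/amber boundary, 15/30 = 50%: exact interval 31.3% to 68.7%, half-width (68.7 − 31.3)/2 = 18.7 points.
- Green boundary, 24/30 = 80%: 1.96 × √(0.16/30) = 0.143, or 14.3 points. The exact interval is 61.4% to 92.3%.

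**Step 4: where ±13 would hold by chance.** Solving 1.96 × √(p(1 − p)/30) ≤ 0.13 requires p(1 − p) ≤ 0.132, so observed adherence of at least about 84% or at most about 16%. The bound therefore depends on the point estimate, contrary to the claim.

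**Step 5: Table 1's denominator taken literally.** If adherence is divided by all 60 consented, n = 60 and 12.65 points is recovered. The largest possible value is then about 30/60 = 50%, the bottom edge of amber. One non-adherent person gives 29/60 = 48.3%, which is red. The green zone cannot be reached. Because the Analysis section requires every criterion to be green before proceeding without adjustment, an overall green could not be reached either.

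**The case against.** The best defence is that the article is consistent on its own terms: Table 1 divides by the number consented, that number is 60, and at 60 the bound holds. This is true of the arithmetic but does not rescue the plan, because on that denominator the adherence criterion could never be green (step 5). The intervention arm is the only workable denominator. The defence does show that both places must be corrected together. Changing the precision statement alone would leave it in conflict with Table 1.

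It can also be said that little turns on the figure. The sample size is attributed first to published guidance, and the traffic-light rule compares percentages with cut-offs without using an interval. Both points stand. They limit the consequence but do not make the stated figure right. Nor could an analysis plan that is not shown put it right, because the figure is printed in the article.

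A reader might go further in four ways that the document does not support.

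- **Recruitment also breaches the bound.** It does not. Its denominator is the number approached, which cannot be smaller than the number consented. With 60 consented, the half-width is at most 12.65 points.
- **The bound fails if fewer than 60 are recruited.** The statement is made for a sample of 60, so a shortfall does not contradict it.
- **Clustering within three groups makes it wrong.** The article gives no intra-group correlation, so any figure would rest on an invented input.
- **The sample of 60 is too small.** The article sets no precision requirement for adherence that 30 people would fail, apart from the ±13 statement itself.

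**Conclusion.** The point holds for adherence only. The claim of at most ±13 points is correct by the normal approximation for recruitment, retention and data completeness. For adherence the worst case is about 5 points wider (17.9 − 12.65 = 5.2), and it is wider again by the exact method. At the green threshold the exact lower limit is 61.4%, well inside amber.

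This assumes that 60 are recruited, that the arms are close to 30 each, and that adherence is judged among those allocated to Sparky Samba. An imbalance of a few people would not change the conclusion. The defect is a misstated precision for one component of the primary outcome, tied to a denominator in Table 1 that cannot work. It does not show that the design or the progression thresholds are unsound.

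**What to change.** Make two linked wording changes.

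1. In Trial design and setting, replace the single bound with, for example:

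> With 60 participants, the half-width of the 95% CI (normal approximation) is at most about 13 percentage points for recruitment, retention and data completeness. For adherence, assessed in the roughly 30 participants allocated to Sparky Samba, it is at most about 18 points (about 19 by the exact method).

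2. In Table 1, change the adherence denominator from the number consented to the number randomised to Sparky Samba, and use the same definition in the Analysis section.

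Naming the interval method matters because the bounds of 13 and 18 hold for the normal approximation and are slightly exceeded by the exact one. The sample size, thresholds and trial procedures do not change. The only cost is that one published precision figure becomes less favourable.
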